## Abstract

**Background:**

Influenza is a global health threat to older adults, and the influenza vaccine is the most effective approach to prevent influenza infection. However, influenza vaccination coverage among Chinese older adults is far less than in developed countries such as the United States (4.0% vs. 64.9%). This study aims to increase influenza vaccination coverage in Chinese adults ≥60 years using a video-led educational intervention conducted by medical students.

**Methods:**

A cluster randomized controlled trial will be conducted in 4 districts of Xi’an city, Shaanxi Province, China, using a stratified sampling approach. Adults aged ≥60 years will be recruited from 8 community hospitals. A self-administered questionnaire of knowledge, attitudes, and practices (KAP) will be employed to record the KAP score. During the 6-month interventional period, participants in the intervention group will receive educational videos focused on influenza and influenza vaccination, coupled with a group discussion conducted by the medical students. For those in the control group, no intervention will be provided. The outcomes measured in both groups will be the influenza vaccination coverage and the KAP scores of all participants.

**Discussion:**

Medical students are more likely to educate older adults about scientific knowledge of influenza and its vaccine compared to clinical practitioners, who, most of the time, remain over-occupied due to the extensive workload. Video-led counseling and education could be a useful option to optimize older adults’ understanding of influenza and influenza vaccination. This eventually could improve the uptake of influenza vaccine among Chinese older adults.

**Trial registration:**

Chinese Clinical Trial Registry; ChiCTR2000034330; Registered 3rd July 2019.

**Supplementary Information:**

The online version contains supplementary material available at 10.1186/s12889-021-10220-1.

## Background

Influenza, an infectious disease caused by the influenza virus, can threaten human health, especially during an influenza pandemic [1]. Every year, 291,243 to 645,832 people die due to seasonal influenza [2]. Influenza related risk of death is higher in older people, such as 84–95% of influenza-associated deaths occur in older adults [3–6].

Influenza vaccination, which is the most effective measure to prevent influenza, can effectively reduce the rate of hospitalization and deaths owing to influenza-associated severe acute respiratory infection [7–9]. Besides, it may produce indirect herd protection for the unvaccinated population in communities [10]. Numerous studies have illustrated influenza vaccination as a cost-effective strategy from the societal perspective to limit influenza progression [11, 12].

In 2019, 18.1% of the total population of China (0.254 billion people) were adults aged 60 years and above [13]. The guidelines for Seasonal Influenza Vaccination in China (2019–2020) [14] recommend that older adults should be prioritized to vaccinate. Nevertheless, the coverage of the influenza vaccine in Chinese older adults remains low (4.0%) than in the United States (64.9%) [15, 16].

Inadequate knowledge, lack of confidence, and complacency (underestimated risk of disease or risk denialism) [17] could be significant reasons for low influenza vaccine coverage among older people in China. A study [18] showed that only 7 and 4% of older adults knew about the influenza virus and vaccine, respectively. In the past, the poor quality of vaccines caused life-threatening effects that lead to several deaths. It diminished the level of confidence about the safety of vaccines among the public [19, 20]. A previous study [18] indicated that more than 55% of the older adults thought they could not get seriously ill from influenza.

The Healthy China Initiative (2019–2030) has emphasized that people should recognize the critical role of vaccines in disease prevention. High-risk groups, including older adults, should get vaccinated before the flu season [21]. Thus, older adults must improve their knowledge, which will increase the uptake of vaccines in the future. Several studies have indicated that educational intervention regarding influenza and its vaccine is one of the practical approaches to enhance community knowledge and confidence [22].

A recent Chinese survey reported that the educational level of two-thirds of older adults is primary school or below [23], which could track to low health literacy, as found in a previous study [24]. Therefore, it may not be suitable to educate older adults through brochures and text messages due to poor health literacy. Still, video-led counseling could be more productive and fruitful in this age group [25]. Medical students, who have relatively abundant knowledge about infectious diseases compared to the public, can communicate with older adults effectively [26]. There are more than three million medical students at different medical schools in China [27]. They have a more flexible time to conduct health education about influenza and influenza vaccines for older people than a clinical practitioner.

This study aims at improving knowledge on influenza and increasing the uptake of influenza vaccination in older adults using a video-led intervention coupled with a group discussion conducted by medical students.

## Methods

### Study design

This is a CONSORT-compliant cluster randomized controlled trial that will determine the effectiveness of video-led counseling to older adults about influenza and influenza vaccination by medical students [28]. Stratified cluster-based sampling will be employed in this study. Based on the socioeconomic status of every district in Xi’an city, Shaanxi Province, four districts will be selected out of 13, including two districts that have high socioeconomic status, including Xincheng and Yanta, and two districts that have low socioeconomic status, including Chang’an and Baqiao. Two community hospitals will be chosen randomly from each district using computer-generated random numbers. In total, 8 community hospitals will participate in this trial (4 hospitals of intervention and 4 hospitals of the control group). The older adults will be chosen randomly by the health management system of Xi’an city. The Chinese guidelines recommend vaccination should preferably be completed by the end of October. If people do not receive the vaccine at that time, vaccination will be available throughout the flu season. Therefore, the intervention period (six months) will have two stages. One is before the flu season (August, September, October), and one is during the flu season (November, December, January).

### Study participants

Eligible old residents attending this program will be screened with the help of the principal investigator and nurses in community hospitals. Inclusion criteria include 1) participants aged 60 years and above; 2) living in the community for the last one year; 3) people willing to participate and provide written informed consent. Exclusion criteria include 1) Those who have cognitive impairment and cannot cooperate; 2) People with serious mental illness. Additionally, those below 60 years of age and who are unwilling to finish the questionnaire will be excluded. A six-item screener will be used to measure the cognitive impairment of potential study participants as it is brief, reliable, and easy to administer [29, 30]. Besides, auditory and visual assessments of the participants will also be conducted.

### Sample size

According to previous studies [31], the influenza vaccine coverage among older adults was almost 2% in western China. The relative risk of intervention ranged from 1.04 to 6.22 in the uptake rate compared to the control group. We hypothesized that the influenza vaccine’s uptake rate would increase from 2 to 10% by employing a medical student-led educational intervention. A mathematical formula [32] was used to calculate the minimum sample size. Eighty participants will be required for each group with a study power of 0.90 and a significance level of 0.05. Considering the loss of follow-up and the low response rate, the sample size will be 200 participants for one group.

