### Randomization

All community hospitals in the four districts will be numbered. Then using computer-generated random numbers, community hospitals will be chosen at random. We will use the community health records management system of Xi’an city to export older adults’ health information of community hospitals and order from 1 to n. Corresponding older people through random number software generating 400 numbers will be selected as a sample. After the older adults are recruited, medical students will choose eligible participants and complete informed consent. Using the knowledge, attitudes, and practices (KAP) questionnaire, baseline information will be collected. On account of balancing the baseline, the clusters will be grouped in the intervention and control group randomly through randomization design and Chi-square test.

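### The stated minimum of 80 per group for 2% versus 10% uptake at 90% power is wrong: those inputs need about 180, and 80 gives about 57% power

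*Protocol article*

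**What the plan says.** The Sample size section of the protocol article takes its control rate from earlier work: "the influenza vaccine coverage among older adults was almost 2% in western China". It cites a range of intervention effects: "The relative risk of intervention ranged from 1.04 to 6.22 in the uptake rate compared to the control group". Its design assumption is that the "uptake rate would increase from 2 to 10% by employing a medical student-led educational intervention".

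The method is cited but not named: "A mathematical formula [32] was used to calculate the minimum sample size". Whether the test is one- or two-sided is not stated. The result is that "Eighty participants will be required for each group with a study power of 0.90 and a significance level of 0.05".

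The enrolment target follows: "Considering the loss of follow-up and the low response rate, the sample size will be 200 participants for one group". No loss or response rate is given. The Randomization section fits that target: "Corresponding older people through random number software generating 400 numbers will be selected as a sample". A group is therefore a trial arm, with 1:1 allocation. The Data analysis section plans a chi-square test of uptake between the two groups.

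**The concern.** The paragraph prints every input that a two-proportion sample size needs, so the result can be checked directly. Eighty per arm looks far too small for an 8-point difference at 90% power: at these rates one would expect 1.6 vaccinated people among 80 controls (80 × 0.02) and 8 among 80 in the intervention arm (80 × 0.10).

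Vaccination coverage is a primary outcome, and this is the only sample size justification in the article. If 80 is wrong, two things follow. A recruitment or follow-up shortfall would be judged against a floor that is too low. A non-significant result could also be taken as evidence of no effect from a trial credited with 90% power that it did not have.

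**Working it through.** **Inputs (Sample size section).** p1 = 0.02, p2 = 0.10, difference 0.08; α = 0.05; power 0.90, so z = 1.2816; equal arms. Sidedness is not stated. Two-sided (z = 1.960) is taken as the main case and one-sided (z = 1.645) is also run. Clustering is ignored throughout, which favours the plan.

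**Attempt to reproduce 80 per group.**

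- *Unpooled variance:* n = (1.960 + 1.2816)² × (0.02×0.98 + 0.10×0.90) / 0.08² = 10.507 × 0.1096 / 0.0064 = 179.9, so **180**.
- *Pooled variance,* mean rate 0.06: n = [1.960×√(2×0.06×0.94) + 1.2816×√0.1096]² / 0.08² = 183.1, so **184**.
- *Pooled with continuity correction:* 207.4, so **208**.
- *Arcsine:* n = 2 × 10.507 / (2·asin√0.10 − 2·asin√0.02)² = 162.4, so **163**.

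| Formula | Two-sided 5% | One-sided 5% |
|---|---|---|
| Unpooled | 180 | 147 |
| Pooled | 184 | 150 |
| Continuity-corrected | 208 | 174 |
| Arcsine | 163 | 133 |

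None gives 80.

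**Would another input explain it?**

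- *Lower power.* At 80% power the range is 122 to 162 two-sided and 96 to 132 one-sided.
- *Larger effect.* The highest relative risk cited, 6.22, gives 0.02 × 6.22 = 12.4% uptake. That needs 128 per group two-sided or 104 one-sided (pooled).
- *Effect that fits 80.* With p1 = 2% and the pooled two-sided formula, the requirement falls to 79 only at about 17% uptake in the intervention arm.
- *A slip in the formula.* The two-sided arcsine figure without its two-sample factor of 2 is 162.4 / 2 = 81. This is a guess, since the formula is not named, and it would not make 80 valid for a comparison of two arms.

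**Power at 80 per group, 2% versus 10%.** With the pooled normal approximation,

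z = [0.08×√80 − 1.960×√(2×0.06×0.94)] / √0.1096 = 0.173, so power = Φ(0.173) = **0.569**.

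Exact enumeration of the uncorrected chi-square test gives 0.570, and Fisher's exact test 0.443. One-sided, the normal approximation gives 0.689.

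**What this does to the 200.** Read as 80 plus an allowance, 200 implies a tolerable loss of 1 − 80/200 = 60%. Against the recalculated minimum, the tolerable loss is:

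- 1 − 184/200 = 8% (pooled, two-sided)
- 1 − 180/200 = 10% (unpooled, two-sided)
- 1 − 163/200 = 18.5% (arcsine, two-sided)
- none with continuity correction, since 208 exceeds 200
- 25% (150, pooled) to 33.5% (133, arcsine) if the test is one-sided

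The same power formula, two-sided, gives:

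| Analysed per group | Loss from 200 | Power |
|---|---|---|
| 200 | 0% | 0.924 |
| 180 | 10% | 0.895 |
| 160 | 20% | 0.857 |
| 80 | 60% | 0.569 |

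**The case against.** The strongest reply is that the trial plans 200 per group, not 80. On the stated inputs 200 gives about 92% power two-sided and 96% one-sided before loss and clustering, so the wrong number is an intermediate step. That holds only if nearly everyone is analysed. The article justifies 200 by expected loss and low response, and the Randomization section draws the 400 numbers before eligibility and consent, so 200 per arm may be the number approached rather than the number analysed.

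Two further points stand in part. The article never says that 60% may be lost; that figure is 80/200 read backwards, and 57% power at that loss is a scenario, not a forecast. The 8% margin depends on the pooled two-sided formula, which is why a range is shown above. Neither point brings the minimum near 80.

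Finally, the cited formula cannot be seen. But every standard two-group version tried, one- or two-sided, needs at least 133 per group at 90% power, and the planned analysis is a between-group chi-square test. Knowing the formula might explain the error but would not remove it.

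**Conclusion.** The figure of 80 per group is wrong for the inputs printed beside it. Two-sided at 5%, 90% power needs about 180 to 184 analysed per group (163 to 208 across formulas); 80 per group gives about 57%. If the test were one-sided, the requirement would be 133 to 174 and the power at 80 about 69%, still well short of 90%.

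The 200 per group does meet the uncorrected requirement under most formulas, with about 92% power if nobody is lost. The apparent 2.5-fold cushion (200/80) is not there: on the pooled two-sided formula the margin is 8%. These figures treat participants as independent, so they are optimistic for a trial with four hospitals per arm. Clustering is a separate matter, and the conclusion here does not need it.

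**What to change.** In the Sample size section:

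1. Remove the statement that 80 per group gives 90% power.
2. Name the formula and the sidedness, and give the minimum they yield: about 184 analysed per group before clustering, for a pooled two-sided 5% test.
3. State the expected response and retention, say whether 200 per group counts people approached, enrolled or analysed, and report the power at the number expected in the analysis: about 92% at 200, about 90% at 180, about 86% at 160 and about 57% at 80, all before clustering.
4. Apply the clustering correction to these figures, not to 80.

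The cost is one rewritten paragraph and a less favourable stated power. This correction does not by itself require more enrolment. It does show how little loss 200 per group can absorb.

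### The 0.90 power claimed for 80 per group does not reproduce, and the rise to 200 makes no allowance for randomising only 8 hospitals

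*Protocol article*

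**What the plan says.** Study design: "This is a CONSORT-compliant cluster randomized controlled trial". Eight community hospitals take part, four in each arm. The Randomization section confirms the unit of allocation: "the clusters will be grouped in the intervention and control group randomly".

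Sample size: the hypothesis is that the "uptake rate would increase from 2 to 10% by employing a medical student-led educational intervention". An unnamed formula leads to this result: "Eighty participants will be required for each group with a study power of 0.90 and a significance level of 0.05". The recruitment figure follows: "Considering the loss of follow-up and the low response rate, the sample size will be 200 participants for one group". The section mentions no intracluster correlation (ICC), cluster size or design effect. The Randomization section gives a total of 400.

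**The concern.** The article sets out a full sample-size argument and gives the reasons for its only inflation step: loss and low response. Clustering is therefore left out of the stated reasoning, not merely cut for length. Participants of one hospital tend to resemble each other, so 200 people in 4 hospitals carry less information than 200 independent people. With 4 hospitals per arm there are also few degrees of freedom for judging the difference.

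Vaccination coverage is a primary outcome, and the Discussion offers the study as a reference for policymakers. If real power is well below 0.90, a null result could be taken as evidence that the education does not work when the trial had little chance of showing that it does.

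**Working it through.** **Inputs from the article.** Control uptake p1 = 0.02; intervention uptake p2 = 0.10; difference 0.08; alpha 0.05; power 0.90; 80 per group raised to 200; 4 hospitals per arm.

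**Assumptions, because the article gives no figure.** Two-sided test; 50 analysed per hospital (200/4); ICC of 0.01 to 0.05, the same in both arms.

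**1. The article's own figure, ignoring clustering.**
- Unpooled variance: 0.02×0.98 + 0.10×0.90 = 0.0196 + 0.09 = 0.1096. Pooled variance: 2×0.06×0.94 = 0.1128.
- n per group = (1.96×√0.1128 + 1.2816×√0.1096)² / 0.08² = 183.1, so 184. The fully unpooled formula gives 180, and a continuity correction gives 208. A one-sided test needs 150.
- Power at 80 per group is 57% two-sided (69% one-sided). None of the standard two-sample formulas tried gives 80 at 90% power.
- Power at 200 analysed per group is about 92%. By the pooled formula it falls below 90% once loss exceeds about 8% (1 − 183.1/200 = 0.084). At 20% loss it is 86%.

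So 200 is close to the minimum for an individually randomised trial with almost no loss.

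**2. Adding the clusters.**
- Design effect DE = 1 + (50 − 1)×ICC. Effective n per arm = 200/DE.
- SE = √(0.1096×DE/200). Ratio λ = 0.08/SE.
- Normal-approximation power = Φ(λ − 1.96). Cluster-level power uses the noncentral t with 8 − 2 = 6 df and noncentrality λ.

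Example at ICC 0.01: DE = 1.49; SE = √(0.1096×1.49/200) = 0.0286; λ = 2.80; Φ(0.84) = 0.80; 6-df power 0.65.

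| ICC | DE | Effective n per arm | λ | Power, normal | Power, t on 6 df |
|---|---|---|---|---|---|
| 0 | 1.00 | 200 | 3.42 | 93% | 81% |
| 0.01 | 1.49 | 134 | 2.80 | 80% | 65% |
| 0.02 | 1.98 | 101 | 2.43 | 68% | 53% |
| 0.05 | 3.45 | 58 | 1.84 | 45% | 34% |

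Using the pooled variance for the test lowers the normal column by about one point (92%, 79%, 67%, 44%). On the normal basis, power falls below 90% once the ICC exceeds about 0.002, even with no loss. If only 80 per arm are analysed (20 per hospital), the 6-df power at ICC 0.01, 0.02 and 0.05 is 39%, 34% and 26%.

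**3. Can larger hospital samples repair it?** As the number per hospital grows without limit, effective n per arm approaches 4/ICC.
- Normal approximation: 4/184 = 0.022 is the largest ICC that allows 90% power.
- 6-df test: 90% power needs λ = 3.91, so the largest ICC is 4×(0.08/3.91)²/0.1096 = 0.015.

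**The case against.** **The ICC is unknown, and the upper end of the range is severe for a rare outcome.** This is fair. A common ICC of 0.015 around a 2% rate implies a between-hospital SD of √(0.015×0.0196) = 0.017, or 86% of the mean. At ICC 0.05 it is √(0.05×0.0196) = 0.031, or 157%. If between-hospital variation were instead proportional to the rate (coefficient of variation 0.4 in both arms), the ceiling would move. A simulation on that basis still gave only about 60% power at 50 per hospital. The ceiling depends on the model; the shortfall at the planned size does not go away.

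**The 6-df test is a choice.** It is, and it alone accounts for the fall from about 93% to 81% at ICC 0. Two hospitals come from each of four districts, so an analysis matched on district would have 3 df and might remove some between-hospital variance. Power could go either way. The normal-approximation figures do not rest on this choice and show the same shortfall.

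**The article plans an individual-level chi-square test, which would reject more often.** True, but that test ignores the clustering, so any gain comes with extra false positives. Power has meaning only for an analysis that respects the 8 hospitals.

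**Two stronger readings are tempting.** A reader might infer that the article claims 0.90 power for 200 per group. It does not: the claim is attached to 80, and 200 is the recruitment figure. A reader might also infer that the 400 random numbers are drawn from one pooled list, so that hospital and arm sizes will be uneven. The Randomization section does not clearly say whether there is one list or one per hospital, Study design describes stratified cluster-based sampling, and Sample size fixes 200 per group. Uneven arms do not follow.

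**Conclusion.** The point holds. The stated 0.90 fails twice: at 80 per group it is about 57% before clustering is considered, and the planned 200 per group has little margin for loss and none for clustering. With 50 analysed per hospital and no loss, power over ICC 0.01 to 0.05 runs from about 80% to 45% by normal approximation and from 65% to 34% on 6 df. These figures rest on the article's 2% versus 10%, a two-sided 0.05 test, equal hospital samples and a common assumed ICC.

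The limit on what larger hospital samples can achieve should be quoted only with its basis: about 0.015 for a 6-df test with a common ICC, about 0.022 by normal approximation. It is not an unconditional property of the design.

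**What to change.** In Sample size, withdraw the 0.90 claim and the figure of 80. Restate power for 4+4 hospitals, giving:
- the number expected to be analysed per hospital after the expected loss;
- a stated ICC range (for example 0.01 to 0.05) and the resulting design effect;
- a small-sample reference, the t distribution with 6 df.

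State that a non-significant result will be read from the cluster-adjusted confidence interval and not as evidence of no effect. In Randomization, it is enough to clarify that about 50 people are drawn from each hospital, if that is the intention.

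This needs no extra participants and no change to the intervention. The downside is a lower stated power. If the sponsor wants to keep 90%, the lever is the number of hospitals. At 50 analysed per hospital, the normal approximation asks for 184×DE/50 per arm: 6 hospitals at ICC 0.01 (184×1.49/50 = 5.5), 8 at 0.02 (7.3) and 13 at 0.05 (12.7). A t reference would ask for somewhat more.
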